**SUSAR EXPEDITED REPORTING**

The sponsor, or whoever assumes the tasks delegated by the sponsor, will notify all suspected SUSARs, to the Ethics Committee within a period of fifteen calendar days from the time of knowing about the event. When the SUSAR has caused the death of the patient or has been life-threatening, the notification shall be made within a maximum period of seven calendar days from the time of knowing about the event. The relevant information concerning subsequent events will be filled in within the following eight days.

## EXPEDITED REPORTING OF OTHER RELEVANT SAFETY INFORMATION

The sponsor, or whoever assumes the tasks delegated by the sponsor, shall notify, as soon as possible and no later than 15 days after having knowledge of it, any information that could alter the benefit/risk relationship of the investigational medicinal product (e.g. an increase in the rate of occurrence of the expected SAR, SUSARs that occur after the completion of a clinical trial, new events related to the conduct of the trial or the development of the investigational medicinal product, any recommendation of the Data Monitoring Committee where relevant for the safety of subjects, etc.

## PREGNANCY REPORTING

Subjects will be instructed to notify the investigator if the subject or partner becomes pregnant.

If any pregnancy occurs during the course of the study, the investigator shall notify the sponsor, or whoever assumes the tasks delegated by the sponsor, within 24 hours of knowing about the event. Also, a follow-up of the pregnancy will be performed to document its outcome and the state of health of the newborn. If the pregnancy outcome meets the SAE criteria or if the newborn presents a serious event, the procedures for reporting an SAE will be followed.

1. **ETHICAL CONSIDERATIONS**

## General Considerations

This clinical study was designed and shall be implemented, executed and reported in accordance with the ICH Harmonized Tripartite Guidelines for Good Clinical Practice, with applicable local regulations ([Law 14/2007](http://www.boe.es/buscar/doc.php?id=BOE-A-2007-12945), July 3^rd^, on Biomedical Research (*Ley de Investigación Biomédica*, BOE 159 of July 4^th^, 2007 and the DIRECTIVE 2004/23/EC OF THE EUROPEAN PARLIAMENT AND OF THE COUNCIL of 31^st^ March 2004 on setting standards of quality and safety for the donation, procurement, testing, processing, preservation, storage and distribution of human tissues and cells) and with the ethical principles laid down in the Declaration of Helsinki.

Before initiating the trial, the investigator/ institution must obtain approval/favorable opinion from the Independent Ethics Committee for the trial protocol, written informed consent form, consent form updates, subject recruitment procedures and any other written information to be provided to subjects.

Prior to the study start, the investigator is required to sign a protocol signature page confirming his/ her agreement to conduct the study in accordance with these documents and all of the instructions and procedures found in this protocol.

Neither patients nor researchers will receive remuneration for their participation in the study.

## Informed Consent

Informed consent must be obtained before conducting any study-specific procedures.

Eligible subjects will be informed before the beginning of the study about the objectives and procedures, as well as the potential risks derived from his/ her study participation.

The process of obtaining informed consent must be documented in the subject source documents.

Women of child bearing potential must be informed that taking the study treatment may involve unknown risks to the fetus if pregnancy were to occur during the study and agree that in order to participate in the study they must adhere to the contraception requirements. Male subjects must be informed that if a female partner becomes pregnant while he is enrolled in the study, contact with the female partner will be attempted to request her consent to collect pregnancy outcome information.

## Data management, confidentiality of trial documents and patients’ records.

The information obtained in this study will be confidential and treated at all times as such.

The handling, communication and transfer of personal data of all the subjects participating in the study will be protected, complying with the basic ethical principles of Biomedical Research and with the applicable regulations: Regulation (EU) 2016/679 of the European Parliament and of the Council of 27^th^ April 2016 on the protection of natural people with regard to the processing of personal data and on the free movement of such data, and repealing Directive 95/46/EC (General Data Protection Regulation) and LAW 41/2002, of 14^th^ November, regulating patient autonomy and rights and obligations of information and clinical documentation.

A CRF must be completed for all patients that have given informed consent.

All entries into the CRF are the responsibility of the investigator or a qualified designated staff member.

Each subject is identified in the study by a Subject Number (Subject No.) that is assigned when the subject is first enrolled for screening and is retained as the primary identifier for the subject throughout his/ her entire participation in the trial. Once assigned, this number must not be reused for any other subject.

Trial records and source documents, including signed ICF, pertaining to the conduct of this study must be retained by the investigator for 25 years from the issue of the final Clinical Study Report/ equivalent summary, in accordance with the applicable regulations (Royal Decree 1090/2015, of 4^th^ December, regulating clinical trials with medicinal products, Ethics Committees for Investigation with medicinal products and the Spanish Clinical Studies Registry).

## Insurance

Insurance coverage is provided for the clinical study.

1. **PRACTICAL CONSIDERATIONS**

## Responsibilities Of Patients

Participants should follow the indications of the Investigator and communicate any eventuality to them. Subjects will be informed of the restrictions that they must adhere to during the trial.

Subjects may voluntarily withdraw consent to participate in the study for any reason at any time. This will not cause a detriment in their clinical follow-up.

If a subject discontinues the study, the investigator will try to ensure that all the needed evaluations to ensure that no adverse event occurs are performed.

## Responsibilities Of The Investigator

Investigators will work in accordance with the national legislation.

Prior to the study start, the investigator is required to sign a protocol signature page confirming his/ her agreement to conduct the study in accordance with these documents and all of the instructions and procedures found in this protocol and to give access to all relevant data and records to monitors, auditors, ECs, and regulatory authorities as required.

## Protocol Adherence

Investigators ascertain they will apply due diligence to avoid protocol deviations. If deviations occur, the investigator must inform the monitor and the consequences of such deviations will be reviewed and discussed among the team. All protocol deviations will be documented/ recorded specifying reason, data, action taken, and consequences in patients and in the study. All documentation related to deviation will be stored in the Investigator File.

## Monitorization, Audit and Inspection

The study will be monitored by SCReN. An appropriate monitoring plan for this study has been developed.

The monitor will visit the site to check the completeness of subject records, the accuracy

of data capture/ data entry, the adherence to the protocol and to Good Clinical Practice, the progress of enrollment, and to ensure that study treatment is being stored, dispensed, and accounted for according to specifications.

The investigator must give the monitor access to all relevant source documents for monitoring activities, audits, EC revisions, and inspections from Health Authorities.

The investigator must maintain source documents for each subject in the study, consisting of case and visit notes (hospital or clinical medical records) containing demographic and medical information, laboratory data, electrocardiograms, and the results of any other tests or assessments. All information on CRFs must be traceable to these source documents in the subject’s file. The investigator must also keep the original informed consent form signed by the subject (a signed copy should be given to the subject).

# Publication Of The Study Protocol And Results

The protocol will be registered in a publicly accessible database. In addition, after study completion and finalization of the study report, the results of this trial will be submitted for publication in a scientific journal or will be made public, complying with the Declaration of Helsinki:

“Researchers, authors, sponsors, editors and publishers all have ethical obligations with regard to the publication and dissemination of the results of research. Researchers have a duty to make publicly available the results of their research on human subjects and are accountable for the completeness and accuracy of their reports. All parties should adhere to accepted guidelines for ethical reporting. Negative and inconclusive as well as positive results must be published or otherwise made publicly available. Sources of funding, institutional affiliations and conflicts of interest must be declared in the publication. Reports of research not in accordance with the principles of this Declaration should not be accepted for publication”.

# Protocol Amendments

The Principal investigator will ensure that the study protocol is strictly adhered to throughout, and that all data are collected and recorded correctly on the CRF.

All protocol modifications must be documented in writing. Any protocol amendment will be identified by a consecutive number, and must be approved and signed by the sponsor and the Principal investigator.

If amendments are relevant, approval by EC must occur before any changes can be implemented.

When the change involves only logistical or administrative aspects of the trial [e.g. change in clinical monitor[s], change of telephone number[s], the EC must be notified.

Amendments that are required for subject safety may be implemented immediately provided the health authorities are subsequently notified by protocol amendment and the reviewing EC is notified.

The protocol amendment can be initiated by either sponsor or by any Principal investigator.

# Ethics Committee (EC)

Before initiating a clinical trial, the investigator/institution must obtain approval from the Ethics Committee in regards to trial protocol, written informed consent form, consent form updates, subject recruitment procedures (eg: advertisements) and any other written information to be provided to subjects.

The ethics committee decision will be provided in writing to the investigator, a copy will be sent to the Sponsor.

The Sponsor will send periodic reports about the clinical trial conduct to the EC, as well as all suspected unexpected serious adverse reactions. The Sponsor will notify the end of the study to the Ethics Committee.

1. **DATA ANALYSIS AND STATISTICAL METHODS**

# General considerations

Tabular summaries will be presented by treatment group.

Categorical data will be summarized by number and percentages. Continuous variables will be summarized by descriptive statistics. Recover incidence (RI): Time to recovery.

The overall survival rate will be calculated by the nonparametric Kaplan-Meier method. Fisher exact test will be used to identify those patient characteristics that are significantly associated with treatment response (complete or partial).

For quantitative characteristics a chi-squared trend test will be conducted to examine whether the proportion of patients responding to treatment either increased or decreased across the levels of the characteristic.

The results of the statistical analysis will be displayed in the tables and as mean ± SD in the Figures. Levels of significance will be expressed as p-values (*p < 0.05).

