## Secondary outcomes:

- Time (days) to normal level of lymphocytes.
- Proportion of patients showing clinical improvement at day 7 according to the investigator (based on respiratory status and blood-result tests).
- Proportion of patients receiving a second cycle.
- Time (days) to first negative SARS-CoV-2 PCR after infusing adoptive NK cells or adoptive memory T cells.
- The incidence of treatment-related adverse events (new or worsening from baseline) will be summarized by system organ class and/or preferred term, severity, type of adverse event and relation to study treatment. They will be defined by the Common Terminology Criteria for Adverse Events (CTCAE) Version 5.0
- Duration (days) of hospitalization.
- Time (days) to discharge or to a NEWS (Appendix 1) of ≤ 2 and maintained for 24 hours, whichever comes first.
- Time to improvement by one category on a 7-point ordinal scale (Appendix 2).
- Subject clinical status (on a 7-point ordinal scale) at day 14.
- Proportion of patients requiring intensive care unit.
- All-cause mortality at Day 28.

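### Minor: the protocol's single figure rule, mean ± SD, does not suit its five time or duration outcomes or its 7-point scale

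*Protocol*

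**What the plan says.** The rules are in the protocol, Data analysis and statistical methods, General considerations.

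- Figures: "The results of the statistical analysis will be displayed in the tables and as mean ± SD in the Figures". No type of outcome is exempted.
- Tables: "Categorical data will be summarized by number and percentages" and "Continuous variables will be summarized by descriptive statistics".
- Censored data: "The overall survival rate will be calculated by the nonparametric Kaplan-Meier method". No method is named for any other time outcome, apart from a fragment that equates recovery incidence with time to recovery.

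The section on secondary outcomes lists five times or durations:

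- "Time (days) to normal level of lymphocytes"
- "Time (days) to first negative SARS-CoV-2 PCR after infusing adoptive NK cells or adoptive memory T cells"
- "Duration (days) of hospitalization"
- time to discharge or a sustained NEWS of 2 or less
- time to a one-category improvement on the 7-point scale

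It also lists "Subject clinical status (on a 7-point ordinal scale) at day 14". In Appendix 2, category 7 of that scale is death. The Follow-up section ends follow-up at Day 90, discharge or death, whichever is first, with telephone contact after discharge.

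**The concern.** A mean ± SD needs a number for every patient. Four of the five times have none when the patient dies, or leaves follow-up, before the event. The figure must then either omit those patients or enter the time of death or censoring as if it were an event time. Omission compares only patients selected by their outcome, so the comparison is no longer the randomised one. Substitution counts a quick death as a quick success.

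Hospital stay differs, because a patient who dies in hospital does have an observed stay. An early death makes that stay short, and in a mean a short stay reads as favourable.

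On the 7-point scale, a mean gives the step into death the same weight as the step off supplemental oxygen.

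At stake is what readers take from the secondary-outcome figures of an open-label trial.

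**Working it through.** The figure rule contains no number to reproduce. The question is whether the rule, followed as written, can mislead. Every rate below is assumed, because the protocol gives none.

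**1. Times with death as a competing event**

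Assume a constant recovery hazard r and death hazard d per day, with follow-up cut at C = 28 days. Write L = r + d and F = 1 − exp(−C·L).

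- Recovered by day C: (r/L)·F
- Dead by day C: (d/L)·F
- Mean time among the recovered: 1/L − C·exp(−C·L)/F
- Mean time to recovery, death or cut-off: F/L

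Let r = 0.06 in both groups and let treatment halve d from 0.02 to 0.01.

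| | SoC (L = 0.08) | Treated (L = 0.07) |
|---|---|---|
| F | 0.8935 | 0.8591 |
| Recovered | 0.75 × 0.8935 = 67.0% | 0.857 × 0.8591 = 73.6% |
| Dead | 0.25 × 0.8935 = 22.3% | 0.143 × 0.8591 = 12.3% |
| Mean among recovered, days | 12.50 − 3.34 = 9.2 | 14.29 − 4.59 = 9.7 |
| Mean to recovery, death or cut-off, days | 11.2 | 12.3 |

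The treated group does better on both recovery and death, yet looks slower on either mean. The last row is also how hospital stay behaves if recovery stands for discharge.

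**2. Range**

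- With equal recovery hazards and d halved, the reversal among the recovered runs from 0.14 day at d = 0.005 (9.97 v 10.11) to 0.98 day at d = 0.04 (8.19 v 9.16).
- It does not depend on the Day 28 cut-off. With C = 90 and d = 0.02 v 0.01, the means among the recovered are 12.4 v 14.1 days, with 74.9% v 85.6% recovered.
- It does depend on treatment not also speeding recovery by much. In this model the mean among the recovered depends only on L. With a recovery hazard ratio of 1.3 and d halved, reversal needs 0.078 + d/2 < 0.06 + d, that is d > 0.036. At d = 0.04 the means are 8.19 v 8.28 days; at d = 0.03 they are 8.66 v 8.52, with no reversal.

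**3. Shrinkage without deaths**

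Take exponential times to PCR negativity with medians of 14 and 21 days, so L = ln 2/14 and ln 2/21. The untruncated means are 20.2 and 30.3 days, a gap of 10.1.

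| Cut-off | Converted | Mean among converters, days | Gap, days |
|---|---|---|---|
| Day 28 | 75.0% v 60.3% | 10.9 v 11.9 | 1.0 |
| Day 90 | 98.8% v 94.9% | 19.1 v 25.4 | 6.3 |

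PCR is scheduled to Day 90, so the second row is closer to the plan. The loss is then far smaller.

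**4. The 7-point scale**

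Take two assumed distributions over categories 1 to 7:

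- Group X: 50, 10, 10, 5, 0, 0, 25%. Mean = 0.50 + 0.20 + 0.30 + 0.20 + 1.75 = 2.95; SD 2.48.
- Group Y: 10, 30, 35, 15, 5, 0, 5%. Mean = 0.10 + 0.60 + 1.05 + 0.60 + 0.25 + 0.35 = 2.95; SD 1.36.

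Deaths are 25% v 5% and discharges 50% v 10%, with the same mean.

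**The case against.** The strongest reply is that the sentence governs figures only. A reader might infer that all results are to be reported as means, and the text does not say that. Tables have their own rules: the 7-point scale can fall under counts and percentages, and the descriptive statistics for continuous data are not confined to means. This stands, and it limits the point to figures.

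Second, nothing in the protocol says that event times will be averaged over patients who had the event, and estimators for secondary outcomes are commonly left to a SAP, which is not at hand here. It is therefore no fault that the protocol names no such estimator. What remains is that it does fix a figure format without exception. A SAP that drew curves or category percentages would depart from that text. Using Kaplan-Meier for survival suggests the authors did not mean the rule for every outcome, but they exempt nothing else.

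Third, deaths are not hidden, because all-cause mortality at Day 28 and need for intensive care are separate secondary outcomes. This is true and lowers the stakes, but it does not make a figure of mean times readable.

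Fourth, a reader might infer from the Day 28 row that a large difference would all but vanish. The Day 90 row shows that this depends on the cut-off, so no such general claim is made.

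**Conclusion.** The point holds as a minor one. The figure rule does not fit the five time or duration outcomes or the 7-point scale. Followed as written, it can shrink a difference or, under some death rates, reverse it. Reversal is possible, not certain: in the examples it is at most about one day by Day 28, and with a recovery hazard ratio of 1.3 it needs a control death hazard above 0.036 per day. These sizes rest on constant, assumed hazards, so the size in this trial is unknown.

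A reader might infer that the trial's main result is at risk. The documents do not support that. The primary outcome is a proportion recovered, compared by chi-square with a covariate-adjusted ratio, and the sample size is built on proportions. Neither uses the figure rule.

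**What to change.** Replace the figure sentence in General considerations with three rules:

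- Use mean ± SD figures only for continuous measures without censoring.
- Show the five time or duration outcomes over all randomised patients as cumulative incidence curves with death as a competing event. For hospital stay, do not count death as a favourable discharge.
- Show the 7-point scale as the percentage of patients in each category, with death visible as its own category.

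Models, contrasts at particular days and summaries of laboratory markers can stay with the SAP.

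The cost is a change of wording and a little more programming. No new data are needed, and the sample size and primary analysis do not change.

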# APPENDIX 1. The NEWS scoring system^24^

The NEWS scoring system is based on a simple aggregate scoring system in which a score is allocated to physiological measurements, already recorded in routine practice, when patients present to, or are being monitored in hospital. Six simple physiological parameters form the basis of the scoring system:

1. respiratory rate
2. oxygen saturation
3. systolic blood pressure
4. pulse rate
5. level of consciousness or new confusion*
6. temperature.

**The patient has new-onset confusion, disorientation and/or agitation, where their mental state was previously normal – this may be subtle. The patient may respond to questions coherently, but there is some confusion, disorientation and/or agitation. This would score 3 or 4 on the Glasgow Coma Score (rather than the normal 5 for verbal response), and scores 3 on the NEWS system.*

A score is allocated to each parameter, with the magnitude of the score reflecting how extremely the parameter varies from the normal value. The score is then aggregated and uplifted by 2 points for people requiring supplemental oxygen to maintain their recommended oxygen saturation.

[figure not shown]

# APPENDIX 3: Declaration of Helsinki

[figure not shown]

#
